**The Protocol**

***1. The objective***

To appraise the efficacy and safety of praziquantel, tribendimidine and mebendazole against the co-infection of helmithes.

***2. The background***

Co-infection with food-borne helminthes (such as *Clonorchis sinensis* , hookworm, *Ascaris lumbricoides* and *Trichuris trichiura*) is common in China. As a subgroup of neglected tropical diseases, these soil-transmitting helminthes infections affect nearly 1.4 billion people worldwide. Among these, approximately 129 million patients are Chinese. Owing to the absence of a vaccine, chemotherapy is commonly used to control the coinfection of helminthes. Thus, the selection of drugs is crucial. As to C. sinensis, praziquantel exhibits satisfactory efficacy and becomes the first line drug of choice for clonorchiasis. The recommended treatment regimen by WHO is 25 mg/kg thrice daily for two consecutive days that results in cure rates of 93.5–100%. However, this dose schedule of praziquantel may be difficult to complete in the mass treatment because of multiple treatments and adverse events, while administration of single dose or reduction of treatment course results in less or unstable efficacy. What’s more, although no praziquantel resistance cases are documented, a low cure rate (29%) reported in Vietnam as patients with C. sinensis infection were treated with three daily 25 mg/kg of praziquantel prompted us to pay more attention to the resistance to praziquantel. Therefore, developing the new drugs against C. sinensis is urgent. In addition, praziquantel also exhibits activity against hookworm and 93% cure rate was reported as a single dose of 40mg/kg praziquantel was administrated to patients with hookworm infection. As to soil-transmitting helminthes, imidazole drugs are recommended for treatment by WHO. Among these, mebendazole is a broad-spectrum antihelmintic agent and was reported to be effective against C. sinensis in rats and their single complete curative dose was 150 mg/kg. Similar results were also reported in Xiao’s study. Tribendimidine is abroad-spectrum anti-intestinal nematodes drug. In recent researches, it is proved to be effective to C.sinensis in rats and hamsters. A single dose of 150 and 100 mg/kg tribendimidine resulted in 98% and 100% mean worm burden reduction in the rats and in hamster, respectively. Meanwhile, tribendimidine showed good effective activity to juvenile C. sinensis in hamsters, and the dose of 100mg/kg tribendimidine caused 90.6% mean worm burden reduction. In addition to these laboratory studies, tribendimidine also showed good therapeutic profiles against C. sinensis and Opisthorchis viverrini in clinical trials, and only mild and transient adverse events were reported. Based on the above evidence, we use the praziquantel, tribendimidine and mebendazole to treat the patients with co-infection of helminthes to appraise the efficacy and safety.

***3. The ethical application***

To apply for approval of ethical verification from the ethical review committee of the National Institute of Parasitic Diseases, Chinese Center for Diseases Control and Prevention with the related supporting information.

***4. The registration of clinical trial***

To register this clinical trial on the website of [www.controlled-trials.com](http://www.controlled-trials.com/)

***5. The procedure***

**(1) The study design**: we will perform a randomized, open-label trial to assess the efficacy and safety of praziquantel, tribendimidine and mebendazole against the co-infection of helmithes. All the participants who meet the eligible criteria will be randomly assigned into four groups: Praziquantel will be administrated orally according to regional policy in Hunan: 75 mg/kg in four divided doses (twice daily spaced by 6 h for two consecutive days). Tribendimidine will be given by two means: one is a single dose of 400 mg and the other is 200 mg twice daily spaced by 6 h. Mebendazole will be given 400 mg as a single dose.

In addition, parts of participants who are assigned to be treated with tribendimidine will accept blood and urine routine checks, hepatic and renal function examinations, and electrocardiogram (ECG) examinations before and 24 h after the treatment. The abnormal indexes will be supervised and recorded.

Participants will be asked to report any potential drug-related signs and symptoms at 3 h, 24 h and 48 h after the first dose by the use of a standardized questionnaire.

Three weeks after treatment, participants were asked for two consecutive stool samples.

**(2) Preliminary survey:** To invite the residents aged 15 to 65 who lives in the Dazhongqiao and Sankoutang village , Qiyang country, Hunan province ,P.R.China to participate this trial. The name, age, sex, educational background, race and telephone will be recorded. Participants will receive containers with unique identification numbers and be invited to bring a fresh stool sample the following morning. Stool containers will then be taken to the laboratory at the Qiyang Center of Diseases Control and Prevention (Qiyang CDC). From each stool sample, three Kato-Katz thick smears will be prepared and be quantitatively examined with light microscopy for worm eggs (e.g., C. sinensis, hookworm, A. lumbricoides and T. trichiura). Number of worm eggs are counted and recorded for each parasite species separately. Patients with a microscopically confirmed co-infection with helminthes will be asked for a second stool sample.

**(3) Sample size.** Sample size was based on a suggested sample size of 12 patients per group for proof-of-concept trials. Taking into account of the patients dropping out, we will plan to enroll 40 participants per group.

**(4) Eligibility criteria**:Eligible for inclusion is all residents of Dazhongqiao village and Sankoutang village aged 15 to 65 years old whose first stool sample to perform the Kato-Katz thick smears in preliminary survey, co-infection with helminthes, and submit the second stool sample and the written informed consent before the treatment.

**(5) Exclusion criteria**: Participants will be excluded from treatment if fulfilling any of the following exclusion criteria: pregnant (for females), the presence of any abnormal medical disorder (i.e., fever and hepatomegaly), history of any acute or sever chronic disease, psychiatric and neurological disorders, and anthelmintic treatment within the previous 4 weeks.

**(6) Informed consent**: Each of the participants will receive a written informed consent. We explain the risk and benefits on the consent form, and tell them all participants are voluntary, and individuals can withdraw from the trial at any time. If the participant is a child, the informed consent should be signed by his/her legal guardian. Written informed consent need to be obtained from each participant or legal guardians of each child before they are allowed to participate this trial.

**(7) The check-up before treatment**: all participants will be required to undergo a inquisitorial medical check-up, and the female participants aged 16 to 50 will accept the pregnancy test. Participant assigned to the two tribendimidine treatment groups will accept blood and urine routine checks, hepatic and renal function examinations, and electrocardiogram (ECG) examinations before the treatment.

Blood samples should be taken immediately to the local hospital with ice packs. Urine samples and part of blood samples should be tested within 30 min as urine and blood routine checks. The other blood samples should be stored at 4 ◦C in the refrigerator for 4 h, and then be centrifugalized. The supernatants will be tested for hepatic and renal function detection.

**(8) Take the medication**: The investigator should give the medication to participants, and ensure they will swallow it with warm water. The participant cannot take any other drugs during the experiment. If the drug is spit out within one hour after taking the medication, he/she will need to take the medication again. Both the strenuous exercise and the drinking will be forbidden during the experiment.

**(9) Follow up:** The trial clinicians will be present, monitor acute adverse events, and provide medical assistance if necessary. Participants will be asked to report any potential drug-related signs and symptoms at 3 h, 24 h and 48 h after the first dose by the use of a standardized questionnaire. Intensity of AEs are recorded and graded as mild, moderate, severe and serious as judged by study physicians.

Mild: asymptomatic or mild symptoms; clinical or diagnostic observations only; intervention not indicated

Moderate: minimal, local or noninvasive intervention indicated.

Severe: severe or medically significant but not immediately life-threatening; hospitalization or prolongation of hospitalization indicated.

Serious: life-threatening consequences; urgent intervention indicated.

**(10) Re-examination of the stool sample**: Three weeks after treatment, participants were asked for two consecutive stool samples. Stool containers will then be taken to the laboratory at the Qiyang Center of Diseases Control and Prevention (Qiyang CDC). From each stool sample, three Kato-Katz thick smears will be prepared and be quantitatively examined with light microscopy for worm eggs (e.g., C. sinensis, hookworm, A. lumbricoides and T. trichiura). Number of worm eggs will be counted and recorded for each parasite species separately.

**(11) Primary and secondary outcomes:** Primary outcomes are the cure rate (CR) and egg reduction rate (ERR) at 3 weeks after treatment as efficacy outcomes. The CR is defined as the percentage of participants excreting eggs before treatment who became negative after treatment. The ERR is calculated as the reduction in the group’s geometric mean egg count after treatment divided by the geometric mean of the same patients before treatment, multiplied by 100. Secondary outcomes are the frequencies of adverse events (AEs) and the abnormal biochemical tests after treatment including urine and blood test, hepatic and renal function examinations and ECG.

**(12) Statistical analysis.** All data will be double entered, and the per-protocol analysis will be pursued. Statistical analyses will be done with SAS software (version 9.1). The numbers of every kind of worm eggs recorded from 6 Kato-Katz slides before and after treatment will be added to calculate the arithmetic mean of eggs per gram of stool (EPG) for every participant. The arithmetic means is used to determine the infection intensity, and the geometric EPG is calculated to assess the egg reduction rate among the treatment groups. Logistic regression models will be used to examine cure rates of helminthes in different treatment groups. Negative binomial regression analysis will be adopted to compare egg reduction rates of helminthes between four groups. Pearson’s χ2 test will be applied to compare the proportion of reported adverse events between the treatment groups. Negative binomial regression models will be used to compare the number of adverse events in the treatment groups.

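### The protocol leaves room for exclusions after randomisation that differ by arm, and the per-protocol-only analysis would carry them into the comparisons

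*Protocol*

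**What the plan says.** Section 5(1) describes an open-label trial and sets the gate to randomisation: "All the participants who meet the eligible criteria will be randomly assigned into four groups". Section 5(4) lists the eligibility criteria: residence in the two villages, age 15 to 65, co-infection on the first stool sample, a second stool sample and written consent.

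Section 5(5) lists the exclusions separately and words them as acting on treatment: "Participants will be excluded from treatment if fulfilling any of the following exclusion criteria". One of them is "the presence of any abnormal medical disorder", with fever and hepatomegaly given as the instances.

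Section 5(7) sets out the pre-treatment check-up. A medical check-up applies to everyone and a pregnancy test to women aged 16 to 50. The next sentence adds tests for some arms only: "Participant assigned to the two tribendimidine treatment groups will accept blood and urine routine checks, hepatic and renal function examinations", and also an ECG. Section 5(1) mentions the same tests before and 24 h after treatment, but for only some of the tribendimidine participants. It says abnormal values are to be watched and noted. Section 5(11) makes post-treatment abnormalities a secondary outcome.

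Section 5(12) names a per-protocol analysis and no other.

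**The concern.** Randomisation protects a comparison only if nobody is removed afterwards for reasons that depend on the arm. Here, two of the four arms are examined more closely between allocation and first dose, by staff who can know the allocation, while a broadly worded exclusion from treatment is still in force. A person with an abnormal liver test or ECG could be found and left untreated under tribendimidine. The same person under praziquantel or mebendazole would not be tested and would be treated.

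With only a per-protocol analysis, anyone left untreated leaves the comparison. The cure rate, the egg reduction rate and the adverse event comparisons would all be exposed, and the per-protocol result alone would not show that it had happened.

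**Working it through.** The plan states no figure on this point that could be reproduced. The check is mainly one of order and wording, followed by a short calculation on assumed values.

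**Order of steps**

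| Step | Section | Who | Timing stated |
|---|---|---|---|
| Eligibility: residence, age, co-infection, second stool, consent | 5(4), used in 5(1) | All | Stool and consent before treatment; eligibility before randomisation |
| Exclusions: pregnancy, abnormal disorder, acute or chronic disease, psychiatric or neurological disorder, recent anthelmintic | 5(5) | All | Excluded from treatment; no link to randomisation |
| Medical check-up, pregnancy test | 5(7) | All; women aged 16 to 50 for the test | Before treatment; order relative to allocation not fixed |
| Blood, urine, liver, kidney, ECG | 5(7), 5(1) | Tribendimidine arms only | Before treatment, after assignment |
| Analysis | 5(12) | Per-protocol | Not applicable |

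1. The 5(4) list that gates randomisation contains none of the 5(5) exclusions. Read literally, a person can be randomised before any exclusion is checked.
2. For the common check-up and pregnancy test, the order relative to allocation is open. For the laboratory and ECG tests it is settled: they are done in people who already have an arm.
3. The stated handling of an abnormal value is to watch and note it. That does not say whether the person is then treated and analysed. The disorder criterion has no laboratory or ECG threshold, either to bring such a result in or to keep it out.
4. A person not treated falls outside a per-protocol set, and no second analysis set is named that would keep the person in.

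**Possible size**

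Let f be the fraction of a tribendimidine arm removed, k the cure rate in those kept and r the cure rate those removed would have had. The cure rate of the whole arm is (1 − f)k + f·r. The per-protocol rate is k. The shift is therefore k − [(1 − f)k + f·r] = f(k − r).

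The arm size of 40 comes from section 5(3). The values of f, k and r are assumptions; the protocol gives none of them.

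| f | Left of 40 | Gap 0 | Gap 10 points | Gap 30 points | Gap 35 points |
|---|---|---|---|---|---|
| 0% | 40 | 0 | 0 | 0 | 0 |
| 5% | 38 | 0 | 0.5 | 1.5 | 1.75 |
| 10% | 36 | 0 | 1.0 | 3.0 | 3.5 |
| 20% | 32 | 0 | 2.0 | 6.0 | 7.0 |

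Worked case: with f = 10%, k = 75% and r = 40%, the whole arm has 0.9 × 75% + 0.1 × 40% = 71.5%. Removal raises this to 75%, a shift of 3.5 points.

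If only some of the arm is tested, as 5(1) says, f falls in proportion. With half tested and 10% of those removed, f = 5% and the shift is 1.75 points. If those removed would have been cured more often than those kept, the sign reverses.

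For scale, the standard error of a 75% cure rate is √(0.75 × 0.25 / 40) = 6.8 points with 40 people and √(0.75 × 0.25 / 36) = 7.2 points with 36.

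**The case against.** The strongest reply is that section 5(1) can be read as full screening before randomisation, with the laboratory and ECG tests serving safety only. Much of this stands.

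- The common check-up carries no reference to assignment: "all participants will be required to undergo a inquisitorial medical check-up, and the female participants aged 16 to 50 will accept the pregnancy test". A reader might infer that all exclusion checks run after allocation is known. The text does not show that; it leaves the order open.
- A reader might infer that abnormal tests exclude people. No section says so. Section 5(1) says they are watched and noted, the tests are paired before and after treatment, and 5(11) uses them as a safety outcome. The instances given for the disorder criterion are clinical signs.
- A reader might infer that different rules apply in different arms. The written rules are the same; what differs is how closely the arms are examined.
- A reader might conclude that the randomised comparison is broken, or tilted towards tribendimidine. Neither follows. Size and direction rest wholly on assumed values, and a 3.5-point shift is about half of one arm's standard error.

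What does not stand is the view that nothing needs changing. Screening before randomisation cannot include tests limited to people already assigned. Noting an abnormal value does not tell staff whether the person remains in the trial, and the named analysis would drop anyone who was not treated.

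**Conclusion.** The protocol permits differential exclusion after randomisation; it does not prescribe it. The wording itself establishes three things: exclusion acts on treatment and not on randomisation, the extra pre-treatment tests follow allocation and are confined to the tribendimidine arms, and the only named analysis is per-protocol. Whether anyone would be removed on these tests is unknown.

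The effect on an arm's cure rate is f(k − r). It is zero if nobody is removed on these tests or if those removed do not differ from those kept. It is 0.5 to 7 points if 5% to 20% of an arm is removed with a gap of 10 to 35 points, all assumed. The point should be corrected because it closes a route to bias cheaply and changes rules that the protocol states; it is more than a request for detail.

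**What to change.** - **Sections 5(1), 5(5) and 5(7):** complete the second stool sample, the medical check-up, the pregnancy test and every 5(5) exclusion for all participants before the allocation is drawn and revealed. Reword 5(5) so that people meeting an exclusion are not randomised.
- **Section 5(7):** state that the tribendimidine-only tests do not decide who is analysed. Anyone left untreated because of them still gives the three-week stool samples, stays in the assigned arm and is reported by arm with the reason. Whether to treat that person remains a clinical decision.
- **Section 5(12):** analyse all randomised participants by assigned arm alongside the per-protocol analysis. Without this change, keeping untreated people in their arm would contradict the current text.
- **Sections 5(1) and 5(7):** reconcile whether some or all tribendimidine participants have the tests.

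The cost is protocol wording and a change in the order of existing steps, with no new test or staff. The small downside is that a few untreated participants may remain in the tribendimidine denominators.

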***6. The second treatment***

Based on first treatment results, we may carry out the second treatment with the same procedure and same clinical practices, hoping to enhance the efficacy.

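### Girls can enrol at 15 but the pregnancy test starts at 16, so a 15-year-old could be treated untested

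*Protocol*

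**What the plan says.** The Protocol sets the enrolment age twice. Section 5(2), on the preliminary survey, plans "To invite the residents aged 15 to 65 who lives in the Dazhongqiao and Sankoutang village". Section 5(4), on eligibility, repeats the range: "aged 15 to 65 years old whose first stool sample".

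Section 5(5) makes pregnancy a reason not to treat and gives no age limit: "Participants will be excluded from treatment if fulfilling any of the following exclusion criteria: pregnant (for females"; other conditions follow in the same list.

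Section 5(7) describes what happens before dosing. It first states that "all participants will be required to undergo a inquisitorial medical check-up", and then, as a separate requirement, that "the female participants aged 16 to 50 will accept the pregnancy test". The laboratory work in the same section (routine blood and urine checks, liver and kidney function, ECG) is for the two tribendimidine groups only, and no pregnancy test is named among it.

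Two other places bear on the point. Section 5(6) foresees participants who are minors: "If the participant is a child, the informed consent should be signed by his/her legal guardian". Section 6 leaves room for a repeat course: "we may carry out the second treatment with the same procedure and same clinical practices".

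**The concern.** The lower age for the test is one year above the lower age for enrolment. A girl of 15 meets the age criterion and is subject to the pregnancy exclusion, but she falls outside the group that is tested.

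The plan's intention is that no pregnant participant receives study drug. For females of 16 to 50 it does not rely on the general check-up to establish this, because it adds a test. It gives no reason why the check-up would be enough at 15. A pregnancy that is unrecognised or not disclosed is what a test picks up and a medical enquiry may miss. At stake is the safety of a small number of minors. Neither efficacy outcome is affected.

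**Working it through.** **Comparison of the age ranges**

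| Rule | Section | Ages covered |
|---|---|---|
| Invitation to the survey | 5(2) | 15 to 65 |
| Eligibility | 5(4) | 15 to 65 |
| Pregnancy excludes from treatment | 5(5) | all females, no limit |
| Pregnancy test | 5(7) | females 16 to 50 |

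Eligible ages minus tested ages leaves age 15 at the lower end and ages 51 to 65 at the upper end. A cut-off at 50 is understandable as the end of childbearing age, and this point does not rely on it. Age 15 has no such explanation.

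**Does anything else close the gap?** The check-up applies to everyone, but the test is named separately from it and with its own age band, so the test cannot be read as part of the check-up. The laboratory checks reach only the tribendimidine groups. No other section mentions a pregnancy test.

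**How many girls could be affected?** The Protocol gives no figure for this, so there is none to reproduce. The inputs are:

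- Planned total: section 5(1) has four groups, and section 5(3) says "we will plan to enroll 40 participants per group", so 4 × 40 = 160.
- Single-year ages in the range: 65 − 15 + 1 = 51.
- Female share *f*: not in the Protocol; assumed 0.5, range 0.4 to 0.6.
- Frequency of age 15 relative to an even spread, *r*: not in the Protocol; assumed 1, range 0.25 to 2.

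Expected number of girls aged 15 = 160 × *f* × *r* / 51. Chance of enrolling at least one = 1 − (1 − *f* × *r* / 51)^160.

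| Scenario | *f* | *r* | Expected number | Chance of at least one |
|---|---|---|---|---|
| Low | 0.4 | 0.25 | 160 × 0.4 × 0.25 / 51 = 0.31 | 0.27 |
| Central | 0.5 | 1 | 160 × 0.5 × 1 / 51 = 1.57 | 0.79 |
| High | 0.6 | 2 | 160 × 0.6 × 2 / 51 = 3.76 | 0.98 |

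These are chances of enrolling a 15-year-old girl, not of treating a pregnant one. The latter needs a pregnancy rate at that age and a miss rate for the check-up, and the Protocol gives neither.

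**The case against.** The best reply is that the sections do not strictly conflict. The exclusion in 5(5) applies to every female, and the test in 5(7) is one way of applying it, used in a chosen age band. A 15-year-old found to be pregnant at the check-up would be excluded, just as a woman over 50 would be. The check-up may also go beyond questions, since other exclusions in 5(5), such as fever and an enlarged liver, are normally found by measurement or examination. The guardian-consent clause in 5(6) does not define a child and would serve equally for participants of 16 or 17. The numbers are small, and section 6 is optional and merely repeats the same gap.

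Much of this is fair as a limit on the point. Whether the check-up amounts to questioning alone cannot be settled from the text; what can be said firmly is that no pregnancy test is specified at 15. The guardian clause is only supporting evidence; the stronger sign that 15 is intended is that it is stated in both 5(2) and 5(4). The 79% must not be read as a risk of harm.

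None of this removes the gap. The plan itself adds a test to the check-up for females from 16, and a site that follows the text exactly will dose a 15-year-old girl without it.

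**Conclusion.** The point holds. As written, the Protocol enrols girls of 15, excludes them if pregnant, and does not test them. The mismatch is a matter of text and depends on no assumption.

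Its size is small: about 1.6 girls of 160 if half the participants are female and ages are evenly spread, and 0.3 to 3.8 over the assumed ranges. How many of these would be pregnant and missed cannot be derived, but it is fewer. If the second treatment goes ahead under the same procedure, the same age limit carries over. Sample size, outcomes and analysis are untouched. The correction should be made because it concerns the safety of minors and costs almost nothing; the validity of the trial does not depend on it.

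**What to change.** In section 5(7), change the lower age for the pregnancy test from 16 to 15, so that females aged 15 to 50 are tested. That matches the enrolment age in 5(2) and 5(4) and would carry over to any second treatment under section 6.

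The cost is one number in the text and at most a few more kits of a test already in use. Because a guardian signs consent for a child, the site should also settle how a minor's result is handled and kept confidential. That question may already arise for tested girls of 16 or 17, if they count as children under 5(6). Nothing changes in the sample size or the analysis.

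### The adverse event question asks about possibly drug-related symptoms although the outcome is all adverse events, which in this open-label trial leaves room for reporting that differs by arm

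*Protocol*

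**What the plan says.** Section 5(1) of the protocol describes the design: "we will perform a randomized, open-label trial to assess the efficacy and safety" of three drugs in four groups. The collection rule for adverse events appears there and again in section 5(9): "Participants will be asked to report any potential drug-related signs and symptoms". Three contacts are set for this, 3, 24 and 48 h from the first dose, and a standardized questionnaire is used. Section 5(9) also provides a second route of observation: "The trial clinicians will be present, monitor acute adverse events, and provide medical assistance if necessary". Study physicians grade the intensity of events. The protocol describes no step in which anyone judges whether an event is related to the drug.

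The outcome sentence on safety in section 5(11) begins "Secondary outcomes are the frequencies of adverse events (AEs" and carries no relatedness condition. Section 5(12) plans a Pearson χ² test to "compare the proportion of reported adverse events between the treatment groups" and a negative binomial model for the number of events.

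**The concern.** The outcome is adverse events, but the question put to participants concerns a subset of them: signs and symptoms that might come from the drug. The two do not match, and the mismatch can be seen in the text without any assumption.

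It matters because of who answers and what they know. Randomisation makes the frequency of symptoms from all causes comparable between arms. It does not do so for symptoms that someone has first sorted by suspected cause, because the sorting takes place after allocation and participants know their regimen. The regimens are visibly different in section 5(1): four doses over two days, two doses in one day, or a single dose. The protocol itself holds different expectations of the drugs. Section 2 gives adverse events as one reason why the WHO-recommended praziquantel schedule may be hard to complete, and reports only mild and transient events for tribendimidine. Some tribendimidine participants also have laboratory and ECG checks 24 h after treatment, a contact not described for the other arms.

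At stake are the absolute adverse event frequencies and the between-arm safety comparison. An analysis plan could not repair this later, because events that were never elicited cannot be recovered.

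**Working it through.** **Step 1: set the sections side by side.**

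| Element | Section | Content |
|---|---|---|
| Asked of participants | 5(1), 5(9) | possibly drug-related signs and symptoms |
| Outcome | 5(11) | adverse events, no relatedness condition |
| Compared between arms | 5(12) | reported adverse events (χ²); number of events (negative binomial) |
| Physician's task | 5(9) | intensity grade; no causality step described |
| Masking | 5(1) | open-label |

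The second row is wider than the first, and nothing in the protocol reconciles them.

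**Step 2: see what a filter does.** The protocol gives no adverse event rate, significance level or power for this comparison, so there is no figure to reproduce. The rest is illustration. From the protocol: n = 40 planned per group (section 5(3)). Assumed: the same true proportion p with an event in two arms (20%, 40% or 60%), the proportion r of those events that is recorded in each arm, and a two-sided 0.05 level.

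Recorded proportion in arm k = p × r_k. Apparent ratio = r₁/r₂, although the true ratio is 1. For example, with p = 0.40 and recording of 100% versus 70%, the recorded proportions are 0.40 × 1.0 = 0.40 and 0.40 × 0.7 = 0.28: a difference of 0.12 and a ratio of 1.0/0.7 = 1.43.

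**Step 3: false-positive rate.** For x and y participants with a recorded event in the two arms and p̄ = (x + y)/80,

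X² = (x/40 − y/40)² / [p̄(1 − p̄) × 2/40].

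The rejection probability is the sum of Bin(x; 40, p·r₁) × Bin(y; 40, p·r₂) over all pairs with X² > 3.841, without continuity correction.

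| Recorded, arm 1 vs arm 2 | Apparent ratio | p = 0.2 | p = 0.4 | p = 0.6 |
|---|---|---|---|---|
| 100% vs 100% | 1.00 | 0.051 | 0.052 | 0.052 |
| 70% vs 70% | 1.00 | 0.054 | 0.049 | 0.054 |
| 100% vs 80% | 1.25 | 0.077 | 0.114 | 0.203 |
| 100% vs 70% | 1.43 | 0.112 | 0.201 | 0.386 |
| 100% vs 50% | 2.00 | 0.247 | 0.497 | 0.796 |

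A normal approximation agrees with the unequal-recording rows to within about 0.03.

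**Step 4: read the table.** A filter of equal strength leaves the test at about its assumed level but lowers the frequencies: at 70% recording, true rates of 20%, 40% and 60% appear as 14%, 28% and 42%. Only a filter that differs by arm creates a spurious difference, and it does so more often as events become more common.

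**The case against.** A reader might infer that drug-related symptoms are all that is captured, that participants decide causality themselves, and that the between-arm comparison is therefore biased. The protocol does not support these statements.

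- **Not the sole route.** Clinicians are present and watch for acute events, so it cannot be said that a symptom blamed on another cause never reaches a physician. This stands. It does not close the gap, however: the sentence concerns acute events, does not say that these observations enter the analysis, and does not describe the clinicians as masked.
- **Self-filtering is inferred.** The standardized questionnaire may be a fixed list put alike to every arm, with the relatedness phrase describing the list and not a judgement by the participant. Its items are not shown, so this cannot be excluded. But a list confined to expected effects could miss unlisted events, so the mismatch with the outcome would remain.
- **Bias is not shown.** Distortion of the comparison needs filtering that differs by arm. The protocol neither shows nor excludes that, and the direction is unknown. The contrast in number of doses also has no force at the 3 h contact: repeat doses on a day are 6 h apart, so every arm has had one administration by then.
- **New wording does not mask anyone.** Unmasked participants can over- or under-report any symptom, and a relatedness field would be completed by physicians not described as masked. This stands too. Neutral wording removes an avoidable filter but not the effect of open-label reporting.

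**Conclusion.** The point holds in a limited form. The elicitation rule is narrower than the outcome it feeds, and in an open-label trial it permits, but does not establish, reporting that differs by arm.

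Two consequences should be kept apart. If a filter operates at all, recorded all-cause frequencies are too low. If it also differs between arms, the comparison is distorted: with a modest difference (100% versus 80%) the false-positive rate is about 0.08 to 0.20, and with 100% versus 70% about 0.11 to 0.39, against about 0.05 with equal recording. These figures rest on the assumed event rates, recording proportions and 0.05 level, on a two-arm comparison within the four-group trial, and on all 40 planned participants per arm being analysed. They show sensitivity and are not estimates for this trial.

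Adverse events are a secondary outcome, and the egg-based primary outcomes are untouched. Safety is nonetheless part of the stated objective in section 1, and the omission cannot be put right after data collection.

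**What to change.** 1. In sections 5(1) and 5(9), replace the relatedness wording with *any sign or symptom since the last contact*.
2. State that the same symptom checklist, followed by an open question, is used in every arm at each of the three contacts.
3. In section 5(9), have the physician who grades intensity also record relatedness, in a separate field.
4. In section 5(12), make events from all causes the main between-arm comparison and physician-judged related events a supplement.
5. Acknowledge that reports come from unmasked participants, so some reporting bias remains.

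The cost is a wording change in two places, one extra form field and a sentence in the analysis section. Stated adverse event frequencies will be somewhat higher. If the existing questionnaire is already a common checklist, item 2 only records current practice.
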